## Abstract

**Background:**

Young adults (15-24 years old) living with HIV may experience pressure both from HIV infection and social role change problems, resulting in a series of psychological problems such as depression and anxiety. Effective psychological intervention can improve their mental health and quality of life.

**Objective:**

The study aims to explore the effectiveness of VR-based mental intervention on young adults living with HIV. The application and advantages of virtual reality (VR) in children’s psychotherapy provide new ideas for psychological intervention for young adults living with HIV.

**Methods:**

We use the qualitative interviews and questionnaire results as well as guided by classical psychotherapy to create a personalized psychological intervention system for young adults living with HIV through VR technology, which is based on the long-term AIDS treatment cohort and infectious diseases cohort of children. We use the mental scales and biochemical indexes as the outcomes, conducting a prospective randomized controlled trial to verify the feasibility and effectiveness of the VR psychological intervention system.

**Results:**

The study began enrollment in September 2023. To date, 160 participants have finished the baseline questionnaires.

**Conclusions:**

The study results might provide a scientific basis for accurate psychological treatment among young adults living with HIV in the future.

**International Registered Report Identifier (IRRID):**

DERR1-10.2196/55633

## Introduction

According to the latest data from the joint United Nations Program on HIV/AIDS (UNAIDS), an average of about 4000 people were newly diagnosed with HIV globally per day in 2021. Young people aged 15-24 years old accounted for 31% of new HIV infections. In the Asia-Pacific region, about 260,000 young people were newly diagnosed with HIV in 2021, accounting for 17.3% of the global increase, second only to Africa [1]. The mental health of people living with HIV/AIDS is an important part of the quality of life, and infection-related stigma makes people living with HIV/AIDS face 2-3 times more anxiety and depression than the general population [2-4]. Young people living with HIV face pressure from social adaptation, such as personal growth and role change, as well as disease pressure caused by the incurability and stigma of HIV infection [5]. Studies on young people aged 10-24 years old living with HIV showed that 21% of them had depression symptoms and 14% had anxiety, and the proportion interval of suicidal ideation was from 4.4% to 24.4%, and those with long-term suicidal ideation ranged from 9.26% to 33.33% [6-9]. So, how to carry out effective psychological intervention for young people living with HIV is very important.

There are many forms of psychological intervention, and numerous interventions are intended to support mental health, mainly by way of face-to-face and group-based intervention, internet intervention, and mobile remote intervention. Regardless of the form of psychological intervention, it is based on the theoretical framework or theoretical basis. Common theoretical bases include cognitive behavioral therapy (CBT) and dialectical behavior therapy (DBT) [10]. Previous studies proved the effectiveness of CBT or DBT in the way of face-to-face intervention. Synder et al [11] conducted a group-based psychological intervention study on people living with HIV aged between 16 and 24 years of CBT. The results showed that the self-perceived social support of the intervention group was higher than that of the control group, but the difference was not statistically significant (*P*=.20) [11]. Bedics et al [12] conducted a 1-year DBT treatment on 101 women with borderline personality disorder, which showed that DBT therapy could reduce suicidal behaviors and nonsuicidal self-injury behaviors. Burton et al [13] conducted a psychological intervention with DBT therapy, suggesting that the depression clinical scores had improved of the participants in the intervention group. DBT therapy has achieved some effects in helping improve behavioral problems in children [14] and alcohol problems among college students [15]. However, face-to-face and group-based CBT or DBT needs to be carried out by professionals, and the existing qualified health care providers and infrastructures are limited in meeting the challenge in China.

Studies in developed countries have shown the feasibility and efficacy of using mHealth to provide counseling and services to improve mental health in diverse populations. Mohr et al [16] conducted a self-control psychological intervention in the general population by mobile phone, and the results showed that depression and anxiety decreased over time [16]. The research team conducted a randomized controlled psychological intervention trial on 300 adults living with HIV on the WeChat public platform. At 3 and 6 months after the intervention, the depression level and suicide ideation rate of the experimental group were reduced compared with the control group (*P*=.02) [17,18]. However, there is no study focusing on mental intervention among young people living with HIV. At the same time, studies showed that compliance with remote Internet or mobile phone intervention is poor, and patients are unable to concentrate during the intervention process, which makes it difficult to ensure the effective implementation of the intervention.

Virtual reality (VR) provides a variety of sensory stimuli to people through the computer-generated virtual environment, enabling people to interact with the virtual environment naturally to achieve a sense of immersion and experience in the real environment [19]. Falconer et al [20] used VR technology to set virtual scenes to treat patients with depression and found that the depression decreased after the intervention, and the improvement effect was still maintained one month after the end of the experiment. Based on the mindfulness-based program (MBP), Modrego-Alarcón et al [21] conducted a study on the stress level of 280 college students through VR equipment. The results showed that the experimental group had increased relaxation and decreased stress levels compared with the control group (*P*=.006) [21]. Navarro-Haro et al [22] combined DBT therapy with VR to guide mindfulness training. The results showed that the impulse to commit suicide, self-harm, give up treatment, and use drugs in the experimental group was reduced after the intervention [22]. However, most of the existing studies are small-scale pilot studies on general adults or adolescents with adverse psychological conditions, and there is little study on young people living with HIV.

In summary, the proposed study intends to address the issues of prevalent mental health problems in young people living with HIV and to innovatively use VR to provide integrated and culturally appropriate intervention for mental health improvement.

## Methods

### Goal and Objectives

The objectives of the project are (1) using DBT as the theoretical framework, based on VR technology to carry out the individualized psychological intervention for young people living with HIV; and (2) A 1:1 prospective randomized controlled trial (RCT) will be conducted to verify the effectiveness of VR psychological intervention on reducing depression and anxiety in young people living with HIV.

### Intervention Design

#### Development of A VR Intervention System

##### Content of the Intervention

The proposed study is guided by DBT and combined with the actual needs and unique characteristics of young people living with HIV to develop a specialized psychological intervention system suitable for the characteristics of this population.

The actual needs of mental health among young people living with HIV were collected based on literature and qualitative interviews with young people living with HIV. The outline of the qualitative interview mainly included (1) basic information and (2) The main source of stress (infection, drug side-effect, income, life expectancy).

Study subjects in the experimental group received 2 modules of psychological intervention. Module 1 was the basic intervention module, mainly the DBT treatment course, which covers 4 parts: mindfulness, distress tolerance, emotional regulation, and interpersonal effectiveness. The second module is a flexible intervention module applicable to the actual needs of young people living with HIV. As shown in Figure 1.

**Figure 1 figure1:**
[figure not shown]
Psychological intervention content in the experimental group. MOOC: Massive Open Online Courses. DBT: dialectical behavior therapy.

##### Intervention Delivery

We set up a user management platform as the support for the intervention. The function of the platform included (1) information management: a complete record with a unique number is generated when each research object is enrolled. The researcher is the system administrator and can add and modify the relevant information of the patient, such as fixed number, basic personal information (deprivatized), clinical and therapeutic information, psychological assessment scale, etc. The system is associated with the VR intervention software, which can record and synchronize the completion of the intervention course of the research object, and the administrator can view and export the corresponding data through the number.

(2) Upload and update intervention resources: the intervention content involved in VR software forms a “resource library” in the management system, and the user portrait is generated when the subject is enrolled in the corresponding intervention content. The user portrait is the virtualization of real users and the category of research objects extracted; that is, the entire psychological intervention system is a big picture. Against this background, different types of subjects receive psychological intervention corresponding to their characteristics to achieve personalized customization. In the course of the experiment, the researchers continuously improved and updated the intervention resources.

(3) The intervention goal setting and process supervision: researchers use motivation type interview (motivational interviewing [MI]) to help subjects set up goals, regularly to supervise the completion of the intervention for subjects, and set a message to remind, intervention to ensure compliance.

##### VR Application Development

VR application development mainly includes 3 stages. First, Scene design is a virtual scene in which the participants experience psychological intervention therapy. This study mainly includes 2 scenes: natural landscape and indoor landscape. The natural landscape was used as the environment for participants to immerse in mindfulness and other skills training. The indoor landscape, including the home environment and the consultation environment, was used for the explanation and learning of psychological intervention courses. Second, regarding interface design, this study follows the principle of consistency of interface structure and style, choosing simple graphical design language and interface style with comfort and color sense. The icon uses a simple 2-dimensional graphic simulation to represent the functional form, which is convenient for the participant to identify and quickly associate the icon function, reducing the possibility of wrong selection. Third, interaction design refers to the use of VR hardware devices such as glasses and gamepads to realize the interaction of subjects in the scene. For example, when the participant enters the “family scene,” he or she can move freely and roam in panorama; through the button control of indoor lighting and curtains, choose the bedroom, living room, consulting room, etc, to carry out the study of psychological courses. As shown in Figure 2.

**Figure 2 figure2:**
[figure not shown]
Virtual reality (VR) system development.

##### Verify the Effectiveness of VR Psychological Intervention

A 1:1 RCT will be conducted to verify the effectiveness of VR psychological intervention in reducing depression and anxiety in young people living with HIV. The RCT was not possible to blind the participants. The study lasted for 12 months. According to the inclusion and exclusion criteria, the participants are randomly divided into an experimental group and a control group. The experimental group received VR psychological intervention for 3 months, and the control group received non-VR mobile phone intervention for the same period. Data will be collected at 5 time points: baseline, postintervention, 3 months, 6 months, and 9 months after intervention, as shown in Figure 3.

**Figure 3 figure3:**
[figure not shown]
The process of the intervention. PHQ-9: Patient Health Questionnaire-9. VR: virtual reality. DBT: dialectical behavior therapy.

##### Measurement

Depression score was measured by the Patient Health Questionnaire-9 (PHQ-9). PHQ-9 is shorter but has demonstrated both good reliability and validity in the Chinese populations [23,24]. The scale consists of 9 items, such as “Little interest or pleasure in doing things” and “Feeling down, depressed, or hopeless,” to measure the depressive status of the participants over the previous 2 weeks. Each item was rated on a 4-point Likert scale ranging from 0 (not at all) to 3 (nearly every day), providing a 0 to 27 total severity score, with higher scores indicating increased depressive symptoms [25].

Anxiety was measured by the Self-rating Anxiety Scale (SAS) that assesses anxiety in the last week with the Chinese version [26,27]. SAS has 20 items with responses of a 4-point Likert scale (1=“never or rarely,” 2=“sometimes,” 3=“most of the time,” 4=“almost every day”). The total score ranges from 20-80, with 50 as a cutoff point, 50-59 being considered mild anxiety, 60-69 as moderate anxiety, and ≥70 as severe anxiety.

##### Study Participants

Inclusion criteria were a positive HIV test, age 15-24 years, depression score (PHQ-9)≥10 (with depressive symptoms), accepting and being able to use VR devices or mobile apps. Exclusion criteria were taking antipsychotic drugs or, for physical or other reasons, being unable to complete surveys or questionnaires independently, or being unable to accept psychological intervention courses.

##### Recruitment

The recruitment location is mainly based on Beijing Ditan Hospital Capital Medical University, which is treating 11,735 people in 2023. After clinic doctors have completed all the treatment procedures, researchers will distribute research leaflets to them to introduce the research project and invite them to participate. If the young people living with HIV agree to participate, the program’s researchers will invite the participants to a separate room to be screened for enrollment conditions.

The staff will present the informed consent form of this study and inform the content of the informed consent form, including the introduction of the project, the benefits and possible risks of participating in this study, and the voluntary principle. The research subjects will be asked to sign the informed consent form after they have fully understood it.

##### Baseline Information Collection

The collection of baseline information in this study included 2 items: filling out questionnaires and retaining biological samples. A self-designed questionnaire was used to collect baseline information, including sociodemographic characteristics, medication and treatment information, clinical indicators, and mental health scale evaluation. The electronic questionnaire data can be downloaded directly, which is convenient to timely grasp or correct the information of infected people enrolled on the same day, and ensure the quality of data. To facilitate data collection, improve work efficiency, and improve data collection quality, electronic questionnaires were used at baseline and 3 follow-up visits.

##### Sample Size Calculation and Group Randomization

The sample size was calculated according to depression, the main outcome indicator of this study. Participants with PHQ-9 depression scale score ≥10 were classified as having depressive symptoms. It is expected that after intervention, the proportion of depression in the intervention group will be reduced by 20% compared with that in the control group. A bilateral test with a sample size ratio of the test group and control group as 1:1, test efficacy (1-β) as 0.9, and α as .05 was adopted, and a loss rate of 20% is expected. Through the calculation of PASS software (NCSS), 145 study subjects need to be included, and finally, 160 study subjects are rounded up, including 80 in the experimental group and 80 in the control group.

To ensure the balance between the experimental group and the control group, the block randomization method was adopted, code was written in R (R Foundation for Statistical Computing), random numbers were generated according to random seeds, and randomization was carried out to make the allocation of each treatment group more balanced and meet the research requirements. According to the order in which the subjects were enrolled, each participant was given a random number generated by the above random scheme. According to the group corresponding to the random number, the subjects were randomly assigned to the experimental group and the control group.

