##### Statistical Analysis

Quantitative data were analyzed using SD or demographic characteristics of composition comparison baseline. The *t* test, ANOVA, or rank sum test were used for hypothesis testing of quantitative data. The chi-square test or Fisher exact probability method was used to test the hypothesis of qualitative data. The effect size would also be calculated. In this study, the intervention effect of the VR psychological intervention system was analyzed using generalized estimating equations (GEE). During the follow-up, the attrition diagram in each group would be plotted over time. In this study, binary classification PHQ-9 is used as the outcome variable, which belongs to longitudinal data, and there is a certain correlation between the data. When conducting statistical analysis of such data, the data correlation should be fully considered. Therefore, GEE was used to analyze the intervention effect to correct for the correlation between data caused by repeated measurements at multiple time points.

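### The 0–27 PHQ-9 score is cut at 10, which is also the entry threshold, so the outcome as stated ignores severity and baseline severity and loses power by an amount that depends on unstated inputs

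*Protocol article*

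**What the plan says.** All references are to the Methods of the protocol article unless stated.

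- **Scale.** Measurement describes the PHQ-9 as "providing a 0 to 27 total severity score, with higher scores indicating increased depressive symptoms". Baseline Information Collection includes the mental health scales, so a baseline score exists for each participant.
- **Entry.** Study Participants requires "depression score (PHQ-9)≥10 (with depressive symptoms").
- **Endpoint for sizing.** Sample Size Calculation and Group Randomization names depression as the main outcome and defines it by the same cut: "Participants with PHQ-9 depression scale score ≥10 were classified as having depressive symptoms". The assumed effect is that "the proportion of depression in the intervention group will be reduced by 20% compared with that in the control group".
- **Effect analysis.** Statistical Analysis says that "the intervention effect of the VR psychological intervention system was analyzed using generalized estimating equations (GEE") and then: "In this study, binary classification PHQ-9 is used as the outcome variable, which belongs to longitudinal data". No covariates are named and none are ruled out.
- **Other tests.** The same section lists tests by data type, among them: "The *t* test, ANOVA, or rank sum test were used for hypothesis testing of quantitative data".
- **Objective.** Goal and Objectives sets out to "verify the effectiveness of VR psychological intervention on reducing depression and anxiety in young people living with HIV". Anxiety is measured by the SAS total, also a quantitative score.

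**The concern.** Because the entry cut and the outcome cut coincide, the binary outcome equals 1 for everyone at baseline. The baseline value of the outcome therefore carries no information and cannot serve as a useful covariate. After baseline, the outcome records only which side of 10 a participant is on. A participant who enters at 10 needs one point of improvement to succeed, while one who enters at 24 and falls 14 points to 10 is a failure. Success thus depends heavily on entry severity, and the stated outcome analysis does not use entry severity.

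At stake is efficiency, not validity. The binary comparison is unbiased under randomisation, but it uses less information than has already been collected. This matters because the Abstract reports 160 completed baseline questionnaires, which equals the target, so precision would have to come from the analysis and not from more recruitment.

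**Working it through.** **1. Inputs from the article.** Two-sided α 0.05, power 0.90, 1:1 allocation, 20% loss, 145 participants rounded up to 160. That is 80 per arm, or 80 × 0.8 = 64 per arm after the planned loss. There are four post-baseline time points (Verify the Effectiveness of VR Psychological Intervention).

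**2. Assumptions, not in the article.** The 20% is an absolute difference; the control rate is 0.50–0.70; the score is normal; the baseline/follow-up correlation r is 0.3–0.5.

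**3. The plan's own figure.** 145 cannot be reproduced uniquely without a control rate. With the pooled two-proportion formula, an absolute 20-point difference and division by 1 − 0.2, it arises at 0.23 vs 0.03 or 0.97 vs 0.77: 58 per arm, 116/0.8 = 145. Control rates of 0.40–0.80 give about 272–325 in total.

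**4. Single visit, 64 per arm.**

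Binary: power = Φ[(0.20 − 1.96·se0)/se1], where se0 is the pooled and se1 the unpooled standard error. At 0.50 vs 0.30: se0 = √(2 × 0.4 × 0.6/64) = 0.0866 and se1 = √((0.25 + 0.21)/64) = 0.0848. Power = Φ(0.357) = 63.9%.

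Score: the same effect on the normal scale is d = z(pc) − z(pc − 0.20), and power = Φ[d·√(64/(2(1 − r²))) − 1.96]. At 0.50, d = 0.524; with r = 0.5, 0.524 × 6.532 − 1.96 = 1.465, so power is 92.9%.

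| Control rate | d | Binary | Score, unadjusted | Score, r = 0.3 | Score, r = 0.5 | Loss vs adjusted score |
|---|---|---|---|---|---|---|
| 0.50 | 0.524 | 63.9% | 84.3% | 87.5% | 92.9% | 23.6–29.0 |
| 0.60 | 0.507 | 62.1% | 81.8% | 85.2% | 91.1% | 23.1–29.0 |
| 0.70 | 0.524 | 63.9% | 84.3% | 87.5% | 92.9% | 23.6–29.0 |

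A simulation with integer scores and baseline truncated at 10 or more (correlation 0.5–0.7 before truncation, control rates about 0.49–0.72, 64 per arm) gave single-visit losses of 21.9–24.7 points. Together these give about 22–29 points.

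**5. Four visits, as the GEE would use.** I simulated 64 per arm with a normal score (no truncation), between-visit correlation 0.5–0.7 and r 0.3–0.5, using each participant's four-visit average as a simple stand-in for the GEE (4,000 replicates per setting).

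| Analysis, constant effect | Power, control rates 0.50–0.70 |
|---|---|
| Binary | 82–91% |
| Binary, adjusted for baseline score | 85–98% |
| Score, unadjusted | 89–96% |
| Score, adjusted for baseline | 93% to over 99% |

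Within each setting the cut alone costs about 5–8 points, and the loss against the adjusted score is about 7–15 points. The truncated integer-score simulation gave 7–8 points at 64 per arm in the settings of step 4, the lower end of that range.

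**6. Waning effect.** If the effect fades after treatment, the loss against the adjusted score is about 9–31 points depending on the settings. With effect fractions 1, 2/3, 1/3 and 0 at the four visits it was 9–28, of which the cut alone accounted for about 5–9.

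**7. Sensitivity to the control rate.** At 0.23 vs 0.03 or 0.97 vs 0.77 with 58 per arm, binary power is 90.3% and score power about 100%, a loss of about 10 points at a single visit.

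**The case against.** The strongest reply is that the planned analysis is a repeated-measures GEE, not a single-visit comparison of proportions. This stands. The 22–29 point figure does not describe the planned analysis; the four-visit figure of 7–15 points does, under a constant effect. Part of that smaller gap is a ceiling effect, but it is still the power the plan would have.

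Second, much of the gain comes from baseline adjustment, which a binary GEE could also use, and the article does not exclude covariates. This also stands, and it is why the cut alone is priced separately at 5–8 points.

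Third, replacing a published primary endpoint late is not free. Baseline enrolment is complete, participants are not blinded, and questionnaires are downloaded on the day of collection (Quality Control). A change made after outcomes have been seen would invite a charge of selective reporting. This limits the fix but does not remove the point.

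Two stronger readings are tempting, and the article supports neither. A reader might infer that anxiety will be tested visit by visit with unadjusted t or rank tests. The sentence on those tests is a generic list by data type, directly after one on baseline comparison, and the GEE is the analysis named for the intervention effect. A reader might also infer that 160 participants cannot give 90% power on the binary outcome. With no control rate this is unproven: 64 per arm gives 92.9% at 0.23 vs 0.03, and four visits give up to about 91% at mid-range rates.

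**Conclusion.** The point holds as one of efficiency. The endpoint as stated discards severity above and below 10, is constant at baseline because entry uses the same threshold, and leaves the collected baseline score unused.

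Relative to a baseline-adjusted analysis of the score, the loss is about 7–15 points of power over the four planned visits under a constant effect, more if the effect wanes, and about 22–29 points at any single visit. All of this rests on an absolute 20-point effect, control rates of 50–70%, a normal score, r of 0.3–0.5 and 64 per arm. None of the control rate, SD or correlation is in the article, so no single figure should be quoted as the loss. Baseline Information Collection speaks of three follow-up visits where the design section implies four after baseline; I used four. The binary analysis remains valid, so this is a recommended improvement, not an error that invalidates the trial.

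**What to change.** 1. Adjust the planned binary GEE for the baseline PHQ-9 total score.
2. In a dated change made before outcome data are examined, pre-specify a longitudinal model of the PHQ-9 total score on the post-baseline visits, adjusted for baseline PHQ-9 (identity-link GEE or a mixed model for repeated measures).
3. If the change can still be made blind to outcomes, make that model primary and keep the proportion at or above 10 as a secondary result. If not, leave the binary endpoint primary and make the score model a key supporting analysis.
4. Use the same form of model, adjusted for baseline SAS, for the SAS score, since anxiety is part of the stated objective and only binary PHQ-9 is named as the GEE outcome.

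**Cost.** No new data, visits or participants are needed. A mean score difference is less direct to interpret than a proportion, which is why the proportion should still be reported. A late change of endpoint must be documented, with its date and a statement of who had seen outcome data by then.

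### The 90% power claim for 145 (rounded to 160) participants rests on an unstated control proportion; 145 is reproduced only near 97% vs 77% or 23% vs 3%, which this design does not support

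*Protocol article*

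**What the plan says.** The section Sample Size Calculation and Group Randomization sizes the trial on depression as a binary outcome: "Participants with PHQ-9 depression scale score ≥10 were classified as having depressive symptoms". The expected effect is that "the proportion of depression in the intervention group will be reduced by 20% compared with that in the control group". The other inputs are two-sided testing with equal allocation, 90% power and a 5% significance level; on attrition, the section says that "a loss rate of 20% is expected". The result, from PASS, is that "145 study subjects need to be included, and finally, 160 study subjects are rounded up", split 80 and 80.

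The section states no expected proportion for either arm, does not say whether the 20% is a difference in percentage points or a relative reduction, and names no test.

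Three other sections bear on what the missing proportion could be:

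- Study Participants makes "depression score (PHQ-9)≥10 (with depressive symptoms" an entry condition, so by the sizing definition everyone is depressed at baseline.
- Verify the Effectiveness of VR Psychological Intervention says that "the control group received non-VR mobile phone intervention for the same period", and sets four post-baseline assessments.
- Statistical Analysis plans a GEE on the dichotomised PHQ-9 across the repeated visits.

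**The concern.** A comparison of two proportions cannot be sized from a difference alone, because the required number depends strongly on where the proportions lie. The article prints a result without this input, so the only check is to solve backwards for the control proportion that yields it. If that value is not credible for the trial's own population, the stated 90% power is not what the design delivers.

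The stake is how the primary result will be read. With 90% power, a null result would count as fair evidence against a 20% benefit of VR over the phone intervention. With power well below that, it would not.

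**Working it through.** **Inputs from the document.** Two-sided α = 0.05 (z = 1.960), power 0.9 (z = 1.282), 1:1 allocation, 20% loss, 20% reduction, N = 145 raised to 160. **Not in the document, so assumed and varied:** the control proportion p1, the absolute or relative reading, and the within-person correlation ρ.

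**Formula (pooled two-proportion test, one time point).**
n per arm = [1.960·√(2p̄(1−p̄)) + 1.282·√(p1(1−p1)+p2(1−p2))]² / (p1−p2)², where p̄ = (p1+p2)/2; then N = 2n/0.8.

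**Step 1: reproduce 145.** After 20% loss, 145 × 0.8 = 116 evaluable, or 58 per arm. On the absolute reading with p1 = 0.97 and p2 = 0.77:

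- p̄ = 0.87; first term 1.960 × √0.2262 = 0.932
- second term 1.282 × √0.2062 = 0.582
- n = 1.514² / 0.04 = 57.3, rounded up to 58; N = 116/0.8 = 145

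By symmetry, 23% vs 3% gives the same answer. The unpooled formula moves the solutions to 96% and 24%, and the continuity-corrected one to 99% and 21%. On the relative reading, 58 per arm needs a control proportion of about 97%.

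**Step 2: the same question for 160.** 160 × 0.8 = 128, or 64 per arm. At 95% vs 75%, or 25% vs 5%, power is 89.6%. So 90% power needs a control proportion of about 95% or more, or about 25% or less.

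**Step 3: compare with the design.** The upper solution needs nearly all controls still at PHQ-9≥10 after three months of a phone intervention, in a sample selected for being above that cut-off, where some will fall below it by regression to the mean. The lower solution needs controls to fall from 100% to about a quarter, and VR to 5% or less.

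**Step 4: power with 160 enrolled, one time point.**
Power = Φ{[|p1−p2|·√n − 1.960·√(2p̄(1−p̄))] / √(p1(1−p1)+p2(1−p2))}.
Example, 60% vs 40%, n = 64: (0.2×8 − 1.386)/0.693 = 0.309, so power is 62.1%.

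| Control | 20 points, 64/arm | 20 points, 80/arm (no loss) | 20% relative, 64/arm | N for 90% (20 points, 20% loss) |
|---|---|---|---|---|
| 40% | 69.9% | 79.4% | 15% | 273 |
| 50% | 63.9% | 73.7% | 20% | 310 |
| 60% | 62.1% | 72.0% | 27% | 325 |
| 70% | 63.9% | 73.7% | 37% | 310 |
| 80% | 69.9% | 79.4% | 52% | 273 |

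At 30% or 90% control, power for 20 points at 64 per arm is about 81.5%. Solving the power formula for the difference at 64 per arm, 90% power is reached at about 27–28 points for control proportions of 50–80%, and about 25 points at 40%.

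**Step 5: the planned GEE.** Averaging m follow-ups with exchangeable correlation ρ multiplies the variance by f = (1+(m−1)ρ)/m, so the effective n per arm is 64/f. For m = 4 and an absolute 20-point gap that is constant over follow-up:

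- ρ = 0.7: f = 0.775, effective n = 82.6, power 73–81% at control 40–80%
- ρ = 0.5: f = 0.625, effective n = 102.4, power 82–88%
- ρ = 0.3: f = 0.475, effective n = 134.7, power 91–95%

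**The case against.** The strongest reply is that 62–70% is not the power of the planned analysis. The article analyses the effect by GEE over repeated visits, and at a correlation of 0.3 four averaged follow-ups bring power above 90% on the absolute reading. This stands as a limit on the conclusion. A reader might infer that the trial has a one-in-three chance of missing the planned effect; that holds only for a single-time-point comparison at assumed control proportions. The reply does not rescue the stated calculation, because the sizing paragraph contains no correlation and no number of repeats, and the gain needs the gap to last to nine months after the intervention.

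A second reply is that the 40–80% control range is not documented. That is correct: no end-of-treatment proportion is given, so the range is an assumption, and power is higher outside it. What the document does supply is the entry criterion and the active control, and these are enough to make about 95% or more, or about 25% or less, hard to defend.

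A third is that no arithmetic slip is shown, since 116/0.8 = 145 works under some inputs. This also stands. The fault is a missing input whose implied value does not fit the design. For the same reason, the text gives no support for reading 145 as a number before loss that was then under-inflated: it is reproduced as already inflated. Reading 145 as a per-arm figure would fit a control proportion of about 44% or 76%, but the 80 and 80 split rules it out.

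Finally, the full protocol may state the proportion. The article nevertheless prints the claim and the result, and they cannot be reconciled with the design as described.

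**Conclusion.** The point holds in this form: 90% power is not supported by what the article states. The figure of 145 needs a control proportion near 97% or 23% (relative reading: about 97%), and 160 needs about 95% or more, or about 25% or less. None of these suits participants who all start at PHQ-9≥10 and whose controls are also treated.

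The shortfall depends on inputs that the authors must supply. Under a single-time-point test, 20% loss and assumed control proportions of 40–80%, power is about 62–70% for 20 points (72–79% with no loss) and about 15–52% if the 20% is relative. With the four-visit GEE, the absolute-reading figure spans about 73–95% for correlations from 0.7 to 0.3. The documents therefore do not support a flat statement that the trial is underpowered by a fixed amount, nor that more patients must be enrolled.

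**What to change.** In Sample Size Calculation and Group Randomization, state:

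- the assumed proportion with PHQ-9≥10 in each arm at the primary time point;
- whether the 20% is absolute or relative, which is for the sponsor to say because the text does not settle it;
- the test to which the power refers.

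Then replace the 90% claim with the power, or the difference detectable with 90% power, that 64 evaluable per arm gives under those inputs. Show the range over control proportions and, if the GEE is the basis, over within-person correlations, with the assumption about how long the gap lasts.

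No extra enrolment is asked for; the Abstract already reports 160 completed baseline questionnaires. The cost is one rewritten paragraph and, probably, a less favourable stated power. It can be done before the analysis.
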